### Random assignment of centres

The eligible centres will be randomised centrally, blindly, and electronically, in the Biocruces-Bizkaia Research Institute, stratified by IHO and in a 1:1 ratio. Therefore, the intervention allocated centres will have access to EMAeHealth, while it will not be accessible for the control group centres. IHOs are groups of health centres within the same geographical area, with similar characteristics and population, under the direction of the same hospital. Therefore, we assume that there are no pre-existing differences in the quality of care provided between centres that belong to the same IHO.

#### Intervention centres

All the patients in these centres, in the first consultation with the midwife, will be informed that EMAeHealth is available to them, and they will be told about the content of the tool. In addition, they will be invited to participate in the study of its clinical effectiveness. If the answer is affirmative, they must sign the consent form and will be provided with a link to the forms (baseline measurements and questionnaires for each measurement) to fill in electronically. Participants sign a consent form approved by the Ethics Committee and can leave the study whenever they want (model consent form as an online supplemental file 1).

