For the study of clinical effectiveness, an active surveillance system will be established to identify eligible patients, who are Spanish-speaking pregnant women attending their first appointment with the midwife between week 6 and 10 of gestation. Regarding their clinical profile, they are low-risk pregnant women. The midwives participating in the study will be in charge of recruiting them consecutively until they have the necessary sample from among the people using and not using the EMAeHealth tool (figure 2).

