#### Control centres

Patients in these centres will not have EMAehealth. They will receive, like the intervention group, the usual care and the possibility of attending ME sessions, but not EMAeHealth. After being informed of the clinical effectiveness study, they will be asked for consent to participate (see online supplemental file 1). Women who sign the consent form for participation in the study will be provided with the link to the forms for each measurement.

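### Intervention-arm women hear about EMAeHealth before they complete the baseline SF-36, from midwives who must know the arm, so consent and baseline can differ between arms

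*Protocol article*

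**What the plan says.** All references are to the protocol article.

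- **Random assignment of centres.** Centres are randomised 1:1 within Integrated Health Organisation (IHO), and access to the tool follows the centre's allocation. The word 'blindly' there describes how centres are assigned. It does not describe how women are recruited or assessed.
- **Methods and analysis, paragraph on eligible patients after Figure 1.** Women are identified at a first midwife appointment in weeks 6 to 10. "The midwives participating in the study will be in charge of recruiting them consecutively until they have the necessary sample". The same sentence goes on: "until they have the necessary sample from among the people using and not using the EMAeHealth tool".
- **Intervention centres.** At the first consultation all patients "will be informed that EMAeHealth is available to them, and they will be told about the content of the tool". The study invitation comes next in the text, introduced as a further step at that visit. If they agree, "they must sign the consent form and will be provided with a link to the forms (baseline measurements and questionnaires for each measurement").
- **Control centres.** "Patients in these centres will not have EMAehealth". On recruitment, this section states: "After being informed of the clinical effectiveness study, they will be asked for consent to participate".
- **Outcomes.** The primary outcome is change in the self-completed SF-36. Measurements are set at weeks 8 and 37 of pregnancy and weeks 1, 6 and 16 post partum. Questionnaires are electronic, and the tool is reached with access codes.
- **Statistical methods.** The main comparison is between intervention and control centres by intention to treat. Adjustment for confounders is mentioned for the per-protocol analysis.

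**The concern.** Randomising centres balances the centres. It does not by itself balance the women who later agree to take part, because each of them is approached after her centre's arm is fixed and by someone who knows it. Two things can then differ by arm.

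The first is who consents. The invitation comes alongside a description of a new tool in one arm and without that offer in the other.

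The second is what the baseline measures. The SF-36 is self-reported, and in the intervention arm it is answered after the woman has heard about the tool. Because the primary outcome is a change, the baseline is half of the endpoint and not merely a covariate. A baseline affected by disclosure passes straight into the treatment comparison. Adjusting for baseline SF-36 would not fully repair it, since the adjusting variable is itself affected. With a target difference of only 2 points, a small distortion is material.

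**Working it through.** **1. Order of events, arm by arm**

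| Step | Intervention centres | Control centres |
|---|---|---|
| Arm known to recruiter | Yes: the midwife presents the tool | Yes: the tool is not accessible there |
| Tool described and offered | Yes, at the first consultation | Not offered |
| Invitation and consent | Same consultation, listed after the tool information | After information about the study |
| Link to questionnaires | After consent | After consent |

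No sentence says that midwives know the arm; this follows from their task. That tool information comes before the invitation is the order of the text only, because the linking phrase does not fix a time sequence. As the visit is written, the tool information belongs to the first consultation and the baseline link is handed over only after consent, so baseline follows disclosure even if the tool information and the invitation were swapped.

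**2. Possible exposure before baseline**

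The first visit falls in weeks 6 to 10 and baseline is set at week 8. If access starts at the visit, a woman seen at week 6 could have the tool for up to 8 − 6 = 2 weeks before baseline. Nothing shown says when codes are issued or ties their release to baseline completion, so this is possible and not established.

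**3. The plan's own sample size (Study size)**

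Inputs: 18 centres per arm, 30 women per centre, SD 10, intracluster correlation 0.01, difference 2 points, alpha 5% (two-sided assumed).

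- Design effect = 1 + (30 − 1) × 0.01 = 1.29
- Standard error of the difference = 10 × √(2 × 1.29 / 540) = 0.691
- Degrees of freedom = 2 × (18 − 1) = 34
- Noncentrality = 2 / 0.691 = 2.893; power from the noncentral t = 80.3%
- With 17 centres per arm, power is 77.8%, so 18 is the smallest number that exceeds 80%

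The stated size reproduces. This point changes no figure in it.

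**4. What a shift would do (illustration)**

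The documents give no size for any shift, so 0.5 and 1.0 point are assumptions. The standard error of 0.691 is carried over to the change score. That assumes the change has the same SD (10) and intracluster correlation (0.01) as the plan uses for the score. Noncentral t, 34 df, two-sided 5%:

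| Spurious shift in change score | Shift / SE | False-positive rate, no true effect | Power if the shift opposes a true 2-point effect |
|---|---|---|---|
| 0 | 0 | 5.0% | 80.3% |
| 0.5 | 0.723 | 10.8% | 55.9% (net effect 1.5) |
| 1.0 | 1.447 | 29.0% | 29.0% (net effect 1.0) |

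The two 29.0% entries agree because a net effect of 1.0 point gives the same rejection probability whether it is all bias or a true 2 points less 1.

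Direction: if hearing about the tool raises baseline answers, change in the intervention arm is understated and power falls. If it lowers them, change is overstated.

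**The case against.** The strongest reply is that the tool is offered to every patient in an intervention centre whether or not she joins the study. A reader might infer that consent in that arm is driven by interest in the tool; the documents do not show this, because consent is to the evaluation and not to access. Control women are also informed of the effectiveness study, and what their consent form says about the tool is in a supplement that is not shown. This weakens the consent argument. It does not remove it, because the invitation is still made in different circumstances.

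A reader might also put a size on selection: suppose 20% of intervention participants differ by a stable 5 points, so the arm mean moves by 0.20 × 5 = 1.0 point. That shift would be in baseline and follow-up alike, and in the stated change outcome it cancels (1.0 − 1.0 = 0). The false-positive rates above apply only to a shift in the change itself, such as one produced by disclosure acting on the baseline answers.

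Third, the phrase about women using and not using the tool could be read as filling the sample by behaviour, contrary to intention to treat. Access by centre allocation, 30 women per centre in 18 centres per arm, consecutive recruitment and the comparison of centres all point to loose wording for the two arms.

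The plan's safeguards are real but do not reach this point. Consecutive recruitment limits a midwife's choice of whom to approach, not who agrees or how she answers. Stratification by IHO balances centres. The flow chart and timetable figures, which might show the order of steps, are not reproduced. They could clarify the sequence written in the text, but the text as it stands needs the change.

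**Conclusion.** The point stands as a design weakness that is cheap to remove. The protocol's visit sequence lets consent conditions differ by arm and places the intervention-arm baseline, part of the primary outcome, after disclosure of the tool. That the midwives know the arm, and that access before baseline is possible, are inferences from the text; the first is unavoidable and the second is open.

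The documents support a risk, not a demonstrated bias, and say nothing about its size or direction. If the change score were shifted by an assumed 0.5 or 1.0 point, a quarter or a half of the 2-point target, the false-positive rate would be about 11% or 29%. The same shift against a true 2-point effect would leave power of about 56% or 29%. These figures rest on the plan's SD and intracluster correlation holding for the change score. Neither selection on tool use nor consent driven by the tool is established.

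**What to change.** - Use one order at the first visit in both arms: the same neutral study information and invitation, then consent, then submission of the baseline forms. Only after that describe EMAeHealth in intervention centres and release the access code. Women who decline get the description and code at once. As forms are electronic and access is by code, release can be triggered by submission.
- Report eligible and consenting women by centre and arm, using the active surveillance system already planned.
- As a wording correction only, in the recruitment sentence after Figure 1, replace the reference to people using and not using the tool with women in intervention and control centres.

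Cost: a small change to the routine first visit, which matters slightly because the trial also studies use under routine conditions; slightly later access for intervention participants; and an ethics notification. The article describes the tool's information area as open to the public, so early exposure is reduced and not excluded. The change has to be made before enrolment, because no later analysis can fully recover a baseline taken after disclosure.

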#### Control centres

Patients in these centres will not have EMAehealth. They will receive, like the intervention group, the usual care and the possibility of attending ME sessions, but not EMAeHealth. After being informed of the clinical effectiveness study, they will be asked for consent to participate (see online supplemental file 1). Women who sign the consent form for participation in the study will be provided with the link to the forms for each measurement.

### Outcomes

Access to EMAeHealth by women and professionals during the study period will be through access codes, which will allow the research team to track the use made by users of the tool while ensuring the confidentiality of the data. It also makes it possible, under safe conditions, to link this use with clinical variables from medical records and with the record of the forms filled in electronically at each measurement.

Results of clinical effectiveness: The primary outcome is change in Health-related quality of life (QoL), measured with the Spanish version of the Short Form 36 (SF-36) questionnaire.^30^ The secondary variables are the number and reasons for visits to the obstetric emergency service and to the health centre for non-pathological pregnancy situations, and the labour stage at the time of going to the hospital for suspected labour onset (measurement is carried out using the Bishop test/dilation in cm, effacement and breaking of waters (YES/NO)). As indirect indicators of autonomy in managing their own health and well-being, self-efficacy for labour and childbirth and self-efficacy in breast feeding will be measured using the Spanish version of Lowe’s CBSEI scales^31^ and the Breastfeeding Self-Efficacy Scale—SF,^32^ respectively.

Measurements of these variables will be performed at weeks 8 and 37 of pregnancy, and at weeks 1, 6 and 16 post partum. Contact with the woman and the response to the questionnaires will be carried out electronically (via mobile phone).

QoL is a parameter that has been defined and recently taken into account as a health indicator by WHO.^33^ The concept of QoL could be defined as an individual’s assessment of their own state in relation to their needs,^33^ so it seems appropriate that it should be the primary outcome measure. The Spanish version of the SF-36 questionnaire has been used to assess the health-related QoL perceived by pregnant women in several studies,^33 34^ showing good psychometric characteristics. The SF-36 questionnaire is made up of eight domains, of which four are oriented towards physical aspects and another four towards mental aspects of health-related QoL. In addition, two summaries are made of this physical and mental component, which explain between 80% and 85% of the variance of the eight domains.^30^ The scores of the questionnaire are transformed on a scale from 0 to 100 points; the higher the score, the better the perception of health-related QoL. A difference of five points in the domain score, or between 2 and 3 points in the summary score is considered clinically relevant.^30^

Self-efficacy is one of the key factors influencing women’s confidence and ability to cope with childbirth, and the Childbirth Self-Efficacy Inventory has been shown to be a valid and reliable instrument to measure maternal confidence in childbirth. The Spanish version of the Childbirth Self-Efficacy Inventory shows adequate psychometric properties (ie, internal consistency and validity). Moreover, self-efficacy is a variable which is sensitive to external modifications, so we believe it may be suitable as one of the secondary measures to assess the effectiveness of using EMAeHealth.

Similarly, breastfeeding self-efficacy is a mother’s confidence in her ability to breastfeed and is highly predictive of breastfeeding behaviours. The Spanish version of the BSES-SF can be considered a valid and reliable measure of maternal breastfeeding self-efficacy.

Indicators of the implementation process: Qualitative indicators: Usability and acceptability of the tool by patients and professionals, as well as barriers and facilitators for its use and adoption in the health system. The qualitative evaluation will be carried out through focus groups of women and professionals, between 6 and 8 per group and as many as necessary until the discourse is saturated.^35^ A semistructured script will be developed for the sessions, based on the theoretical constructs of the CFIR,^28^ which will also serve as the basis for the analysis. The CFIR includes 37 constructs within 5 main domains: intervention characteristics, outer setting, inner setting, individual characteristics and implementation process. Overall, the CFIR aims to help identify potential factors (ie, barriers and facilitators) that are believed to influence implementation. Sessions will be audiorecorded and moderated by an expert in qualitative techniques while an assistant will take notes. Later the sessions will be transcribed and analysed. Quantitative indicators: adoption and frequency of the use of EMAeHealth and its areas according to stratification profiles and correlates with other variables (indicators: patients exposed to the digital tool, by centre and group; women with access to EMAeHealth who access the tool once; frequency of use of the tool, frequency of use of the different functions of the tool, etc).

Predictive, modifying and confounding variables: Patients: Age, parity, nationality, race, social class, educational level, marital status, work situation, distance to hospital, spontaneous pregnancy versus assisted reproductive technique, obstetric history and other clinical characteristics. Professionals: Sex, age, length of time in the position, type of contract, profile of adoption of innovations by professionals, measured by means of a questionnaire by Borracci *et al*, 2013.^36^ Health centres: reference IHOs, number of midwives and participation rate, rural or urban environment, and population served (figure 3).

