### Statistical methods

EMAeHealth clinical effectiveness results: quantitative comparisons will be made between intervention and control centres, with an intention-to-treat approach. Mixed models (linear or generalised as appropriate to the variable under study), which take into account the hierarchical structure of the data (patients grouped by midwives, midwives grouped by centre), will be used and 95% CIs will be calculated. Likewise, per-protocol analysis will be carried out, in which the effectiveness of the express use of both the tool in general and in particular of some of its components will be evaluated, adjusting for possible confounding factors. Statistical analysis will be carried out by a professional who is not part of the research team.

Implementation process: For the qualitative evaluation of the tool and its implementation, the analysis of the focus groups, facilitated by the ATLAS.ti software programme, will be structured in three phases: a deductive analysis to determine which CFIR constructs influence its use in real life, followed by an inductive analysis to identify others not included in the CFIR framework that could influence its use, and a third validation phase using triangulation. The analysis results report will be provided to each patient and professional, who will have the opportunity to provide feedback to the team of analysts with their comments (‘response validity’).

For the quantitative evaluation, the distribution of the indicators associated with the use and scope of the tool as well as its components will be described. Measures of central tendency, dispersion and proportions will be calculated, with 95% CIs, and the relationship between the indicators and the predictor/confounding variables will be analysed using mixed models.

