#### Study size

For the clinical effectiveness study, 18 centres will need to recruit 30 patients each, in each arm of the study (N=1080). This will make it possible to detect a difference of two points as significant in the mental component of the SF-36 test, with an alpha error of less than 5% and power greater than 80%. A 10-point SD is assumed for the mental SF-36 and an intracluster correlation of 0.01.

The calculation took into account the cluster design of the study and it was carried out using the National Institute of Health GRT sample size calculator* which assumes that the analysis will employ mixed-model regression methods.

* Research Methods Resources: National Institutes of Health. (Accessed on 2 January 2020). Available from: https://researchmethodsresources.nih.gov/grt-calculator

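### The primary outcome is worded as change in SF-36, but power rests on the SD of the score with no correlation stated; adjusting for the week-8 score resolves this at N=1080

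*Protocol article*

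**What the plan says.** All references are to the protocol article.

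- **Outcomes.** "The primary outcome is change in Health-related quality of life (QoL"), measured with the SF-36. No start or end visit is given for the change. The schedule follows: "Measurements of these variables will be performed at weeks 8 and 37 of pregnancy, and at weeks 1, 6 and 16 post partum".
- **Study size.** Target power is above 80%, at an alpha below 5%. The trial is sized to "detect a difference of two points as significant in the mental component of the SF-36 test". The inputs are: "A 10-point SD is assumed for the mental SF-36 and an intracluster correlation of 0.01". The size is given as "18 centres will need to recruit 30 patients each, in each arm of the study (N=1080"). No SD of change and no correlation between visits is stated.
- **Statistical methods.** The intention-to-treat comparison uses "Mixed models (linear or generalised as appropriate to the variable under study), which take into account the hierarchical structure of the data", that is, women within midwives within centres. The week-8 score is neither included in that model nor excluded from it. Adjustment for confounders is mentioned only with the per-protocol analysis.

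**The concern.** A score and its change have different SDs. With equal variances at the two visits, they coincide only when the correlation between the visits is 0.5. Read as written, the article powers one quantity and declares another to be the primary outcome. The stated power therefore carries over to a simple change score only under a condition on r that the article does not give.

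The calculation also has almost no margin at an SD of 10, so a modest rise in the SD takes power below 80%. The schedule runs from early pregnancy to 16 weeks after birth, and the article gives nothing that would show r to be above or below 0.5 over that interval.

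The second issue is efficiency. The week-8 SF-36 is already collected. Using it as a covariate is more precise than subtracting it, whichever side of 0.5 the correlation falls on.

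**Working it through.** **Inputs from the article.** Difference 2 points; SD 10; ICC 0.01; 18 centres of 30 women per arm (540 per arm); allocation "stratified by IHO and in a 1:1 ratio"; alpha 5%. The article does not state sidedness, so I take it as two-sided.

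**Assumptions.** The correlation r between the week-8 score and the follow-up score is not given, so I show a range. Variances are taken as equal at both visits, with the same r at woman and centre level, and the ICC is 0.01 for every version of the outcome.

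**Step 1: the plan's own figure.**
- Design effect = 1 + (30 − 1) × 0.01 = 1.29.
- Effective n per arm = 540 / 1.29 = 418.6.
- SE = 10 × sqrt(2 × 1.29 / 540) = 0.691.
- Noncentrality = 2 / 0.691 = 2.89.
- Power from the noncentral t with 2 × (18 − 1) = 34 df is 80.3%. The normal approximation gives 82.5%.
- With 17 centres per arm, t-based power is 77.8%, so 18 is the smallest number that reaches 80%.

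The stated figure reproduces on its own inputs.

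**Step 2: the two analyses.**
- Simple change to one visit: SD = 10 × sqrt(2(1 − r)).
- Follow-up score adjusted for week 8: SD = 10 × sqrt(1 − r²).
- Ratio of variances, change to adjusted = 2(1 − r) / (1 − r²) = 2 / (1 + r).

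Putting each SD into the formula of step 1:

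| r | SD, change | Power, change | SD, adjusted | Power, adjusted | Variance ratio |
|---|---|---|---|---|---|
| 0.2 | 12.65 | 60.4% | 9.80 | 81.8% | 1.67 |
| 0.3 | 11.83 | 66.1% | 9.54 | 83.8% | 1.54 |
| 0.4 | 10.95 | 72.8% | 9.17 | 86.6% | 1.43 |
| 0.5 | 10.00 | 80.3% | 8.66 | 90.1% | 1.33 |
| 0.6 | 8.94 | 88.2% | 8.00 | 94.0% | 1.25 |
| 0.7 | 7.75 | 95.2% | 7.14 | 97.6% | 1.18 |

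With 30 women per centre, 80% power for the simple change score needs 25 centres per arm (N=1500) at r = 0.3 and 22 (N=1320) at r = 0.4. The adjusted analysis needs 17 (N=1020) and 16 (N=960).

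**Step 3: different correlations at the two levels.** Write rc for the correlation of centre means, keep r for women, and set SE² = (2 × 100 / 18) × (0.01 × fc + 0.99 × fi / 30). For the change score, fc = 2(1 − rc) and fi = 2(1 − r). For adjustment with one common slope, fc = 1 + r² − 2·r·rc and fi = 1 − r². At r = 0.5, change-score power is 71.6% if rc = 0 and 87.6% if rc = 0.9. Adjusted power is 85.5% and 93.4%. The 0.5 threshold moves, but adjustment stays ahead.

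**Step 4: change averaged over visits.** If change meant the mean of the four later scores minus week 8, with r equal between all pairs of visits, its variance would be 100 × [(1 + 3r)/4 + 1 − 2r] = 125(1 − r). The SD would then exceed 10 only for r below 0.2. Power would be 85% at r = 0.3 and 90% at r = 0.4.

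**The case against.** The strongest reply is that the article does not commit to the weaker analysis. A condensed article gives the model class and the clustering levels and leaves covariates to the analysis plan. Tying confounder adjustment to the per-protocol comparison is natural, because use of the tool is not randomised. A reader might infer that the intention-to-treat model has no baseline term. The text does not support that inference: it is silent, and a longitudinal mixed model that uses the week-8 score would fit everything it says. This part of the reply stands.

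A reader might also infer that the trial is underpowered or that N=1080 is wrong. The documents do not support that either. The figure reproduces, r appears nowhere, and above 0.5 a simple change score exceeds the planned power. The single-visit change from week 8 is itself an inference, and step 4 shows that averaging the later visits lowers the threshold to 0.2. Nor is an unadjusted change score biased under proper randomisation; what is lost is precision.

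The claimed gain from adjustment also needs two limits. That it never loses precision is a large-sample statement: a covariate costs a degree of freedom, which is trivial with 1080 women and 36 centres unless r is close to zero. And under Intervention centres, women hear of the tool at the same consultation at which those who consent are given the link to the forms. The article does not establish that the week-8 score precedes knowledge of allocation or access to the tool.

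The reply does not remove the mismatch in wording. The outcome is fixed as change, the SD is that of the score, and no correlation links them. If an analysis plan adds the baseline term, the Study size paragraph still needs to say what its SD describes.

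**Conclusion.** The point holds as a mismatch to reconcile and a nearly free gain in precision, not as an error in the sample size. The stated power is correct for an outcome with an SD of 10. For a simple change from week 8 to one visit, it requires r of about 0.5 or more; power runs from 60% at r = 0.2 to 95% at r = 0.7. The adjusted analysis runs from 82% to 98% over the same range and does not fall below 80.3% at any r, leaving aside the negligible cost of one covariate, so it supports N=1080 without an increase. These figures rest on equal variances, the same r at both levels, an unchanged ICC of 0.01 and 30 women analysed per centre. The correlation is assumed throughout. The change should be made, but nothing here shows that the trial as planned would miss its target.

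**What to change.** 1. In Outcomes, define the primary outcome as the SF-36 mental component score at one named follow-up visit.
2. In Statistical methods, estimate the arm difference in the mixed model with the week-8 score as a covariate. A constrained longitudinal model with a common baseline mean in both arms and a level for repeated measures within women is an alternative; it also keeps women without a baseline form.
3. In Study size, state that the SD of 10 is that of the score, and give the assumed correlation with week 8 and the resulting power. N=1080 can stay.
4. State that the week-8 form is completed before access to the tool is given, so that the covariate is a true pre-intervention value.

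The cost is a few sentences and one covariate. No new measurements and no additional women are needed. The one practical demand is the order of events at the first consultation in item 4.
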